## Methods

### Study Design

This is a 2-arm, parallel-group, superiority RCT with random allocation in a 1:1 ratio to the intervention and control groups (Figure 1).

**Figure 1. F1:**
[figure not shown]
CONSORT (Consolidated Standards of Reporting Trials) flow diagram of the study. CF: complementary feeding; EBF: exclusive breastfeeding; EIBF: early initiation of breastfeeding; IYCF: infant and young child feeding; MAD: minimum acceptable diet; MDD: minimum dietary diversity; MFF: minimum meal frequency; mHealth: mobile health.

### Study Setting and Duration

The trial will be conducted at the Women and Child Secondary Care Hospital, affiliated with the Aga Khan University Hospital (AKUH), located in the Kharadar area of Karachi, Sindh. The trial is planned to commence in February 2026 and will likely end in May 2027.

### Study Participants

#### Inclusion Criteria

Inclusion criteria were as follows: women aged 18 years or older, at 36±1 weeks of gestation, with a singleton pregnancy without risk factors, registered for delivery at the study sites, planning to stay in their respective areas for at least 1 year postdelivery and to register for child immunization at associated Family Health Centers, owning smartphones with internet access, able to read Urdu, and providing consent for participation.

#### Exclusion Criteria

Exclusion criteria were as follows: high-risk pregnancies, including maternal neurological, heart, autoimmune, or renal disease, preeclampsia, placenta previa, multiple gestations (twins/triplets), fetal structural or genetic anomalies, fetal growth restriction, and birth trauma requiring neonatal intensive care unit admission, women who require referral, and women who plan to move to a different residential area after delivery.

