### Randomization and Allocation Concealment

Participants will be randomly assigned in a 1:1 ratio to the intervention or control arm using a computer-generated block randomization sequence prepared by the AKUH Clinical Trials Unit. Allocation concealment will be ensured using opaque, sealed, and sequentially numbered envelopes containing group assignments. The envelopes will be opened sequentially after participant enrollment to ensure concealed allocation and minimize selection bias.

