### Blinding and Bias Minimization

Due to the nature of the intervention, blinding of participants and the RA is not feasible. To minimize observer and reporting bias, standardized outcome assessment procedures will be implemented across both study arms. The RA will receive training on neutral interviewing techniques and adherence to standardized counseling scripts to reduce differential probing or influencing participant responses. Structured questionnaires will be used to ensure consistency and reduce subjective interpretation during outcome assessment. In addition, data analysis will be conducted using coded group allocation to minimize analytical bias.

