#### Message Schedule

Messages will be delivered 3 times per week, beginning in the predelivery period and continuing until the child reaches 12 months of age. This schedule ensures continuous exposure to age-appropriate information during pregnancy and early infancy.

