#### Application Onboarding

At enrollment, the RA will install the app on the smartphones of participants randomized to the intervention arm and provide a hands-on demonstration of its functionality to ensure correct initial use. To further optimize intervention adherence, participants will receive automated in-app notifications informing them of newly released content, along with reminder messages if content remains unaccessed for 48 hours. These prompts are intended to minimize missed exposure and sustain consistent engagement with the intervention over time.

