### Statistical Analysis

#### Data Analysis Plan

Baseline characteristics will be summarized by randomized group using frequencies and percentages for categorical variables (eg, education, socioeconomic status, area of residence, and employment status) and mean (SD) or median (IQR) for continuous variables (eg, maternal age and parity), as appropriate. Normality of continuous variables will be assessed using the Shapiro-Wilk test. Baseline comparability will be evaluated using chi-square or Fisher exact tests for categorical variables and independent-samples *t* tests or Mann-Whitney *U* tests for continuous variables.

All primary and secondary analyses will follow the intention-to-treat principle, including all participants as randomized. Primary outcomes (EBF and AACF at 6 mo of infant age) are binary and will be analyzed using regression models appropriate for dichotomous outcomes. The results will be expressed as adjusted risk ratios or odds ratios with 95% CIs. Treatment effects will be reported with corresponding 95% CIs and 2-sided *P* values. Repeated measures of EBF (at the 6th, 10th, and 14th weeks) and CF practices will be analyzed using mixed-effects regression models with random intercepts to account for within-participant correlation and fixed effects for treatment group, time, and group-by-time interaction.

Secondary outcomes that are binary, including EIBF, continued breastfeeding at 1 year, MDD, MMF, and MAD, will be analyzed using similar logistic regression approaches. Continuous secondary outcomes, including mean duration of breastfeeding and child anthropometric *z* scores (height-for-age, weight-for-height, and weight-for-age), will be analyzed using linear regression or linear mixed-effects models, with results reported as mean differences and 95% CIs.

Breastfeeding self-efficacy and mHealth usability will be measured using validated multi-item Likert-scale instruments. Composite scale scores will be generated by summing or averaging item responses and analyzed as continuous outcomes using linear or mixed-effects linear regression models, as appropriate. Distributional assumptions will be assessed, and robust standard errors or nonparametric methods will be applied in sensitivity analyses if substantial departures from normality are observed.

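### One exclusion criterion is a birth event that cannot be known when women are randomized in late pregnancy, so it either never operates or conflicts with the intention-to-treat rule

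*Protocol article*

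**What the plan says.** All references are to the protocol article.

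- **Inclusion Criteria:** enrolls "women aged 18 years or older, at 36±1 weeks of gestation", that is, before delivery.
- **Exclusion Criteria:** lists high-risk pregnancies, preeclampsia among them, and also "and birth trauma requiring neonatal intensive care unit admission, women who require referral". No time point is attached to any item.
- **Table 2:** ticks eligibility screen, consent and randomization once, in the Baseline column, which precedes the Birth column.
- **Randomization and Allocation Concealment:** "The envelopes will be opened sequentially after participant enrollment".
- **Application Onboarding:** "At enrollment, the RA will install the app on the smartphones of participants randomized to the intervention arm".
- **Message Schedule:** messages run "beginning in the predelivery period and continuing until the child reaches 12 months of age".
- **Blinding and Bias Minimization:** "blinding of participants and the RA is not feasible".
- **Data Analysis Plan:** "All primary and secondary analyses will follow the intention-to-treat principle, including all participants as randomized".

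The article does not say who applies the birth-trauma criterion, when it is applied, or whether such a dyad stays in follow-up and analysis.

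**The concern.** An exclusion criterion should be decidable before allocation. Whether birth trauma will lead to NICU admission is not decidable at 36±1 weeks. If the criterion is used at all, it is used on a dyad that already has an arm, has received baseline counseling and, in the intervention arm, has the app and its predelivery messages.

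The event is also tied to a primary outcome. An infant admitted to NICU is plausibly less likely to be exclusively breastfed. Dropping such infants raises the observed EBF rate in the arm that loses them, and unequal dropping shifts the between-arm difference. Dyads classed as excluded might also not be counted as missing. They would then escape both the 10% trigger for multiple imputation and the attrition handling under Retention Strategy. If follow-up stops when a dyad is excluded, no later analysis rule can recover its 6-month outcome.

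**Working it through.** **1. The two readings of the criterion**

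| Reading | Consequence |
|---|---|
| Applied at the baseline screen, as Table 2 implies | The event has not happened, so nobody can meet the criterion and it has no effect |
| Applied at or after birth, when it becomes knowable | A randomized dyad is removed, contrary to the Data Analysis Plan |

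The item is wrongly fixed on either reading.

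**2. Which items are affected**

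- Birth trauma with NICU admission: certainly after randomization.
- Referral: no time point. It can be a need known at enrollment, and is a problem only if applied later.
- Preeclampsia: can be assessed at 36±1 weeks, so it is a valid baseline screen.

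**3. The plan's sample size, for context**

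Inputs from Sample Size: EBF 48% vs 68%, complementary feeding (AACF) 50% vs 70%, two-sided 5%, 80% power, 1:1, 20% loss. With p̄ the mean of p1 and p2:

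n per arm = [1.96·√(2p̄(1−p̄)) + 0.842·√(p1(1−p1)+p2(1−p2))]² / (p2−p1)²

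- EBF: 95, and 95/0.8 gives 119 per arm (238 total). With continuity correction: 105, then 132 (264 total).
- AACF: 93, then 117 (234 total). With continuity correction: 103, then 129 (258 total).

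The stated 300 is not reproduced exactly. It is larger than each of these, so the statement that it suffices is true.

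**4. Effect of removal on power**

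The removal rate e is not in the documents; 2-15% is an assumption. Evaluable n per arm = 150·(1−e)·0.8.

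| e | n per arm | Power EBF | Power AACF |
|---|---|---|---|
| 0 | 120 | 88.6% | 89.0% |
| 2% | 118 | 87.9% | 88.4% |
| 5% | 114 | 86.9% | 87.4% |
| 10% | 108 | 85.1% | 85.6% |
| 15% | 102 | 83.0% | 83.5% |

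**5. Effect of removal on the EBF comparison**

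Assume no treatment effect, overall EBF of 48% in both arms, and EBF of q among removed dyads. The rate among those left is f(e) = (0.48 − e·q)/(1 − e).

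| Removed, one arm vs other | q = 20% | q = 30% |
|---|---|---|
| 5% vs 5% | 0 | 0 |
| 5% vs 10% | 51.1 − 49.5 = 1.6 points | 50.0 − 48.9 = 1.1 points (1.05 before rounding) |
| 2% vs 10% | 51.1 − 48.6 = 2.5 points | 50.0 − 48.4 = 1.6 points |

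The sign follows the arm that loses more dyads.

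**6. How likely such a gap is by chance**

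If each dyad has the same probability e of removal in both arms, the SD of the between-arm difference in removal is √(2e(1−e)/150). This is 2.5 points at e = 5% and 3.5 points at e = 10%. A 5-point gap is then 1.4 to 2 SD. A 10-point gap is about 3 to 4 SD.

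**The case against.** The strongest reply is that no sentence in the article says a randomized dyad will be dropped. Table 2 screens once, at baseline, and the only analysis rule stated is intention-to-treat. Read literally, the birth-trauma item is dead text, and the full protocol, which is not shown, may say how such dyads are handled. The first half of this stands: the conflict with intention-to-treat arises on one of the two readings. But the timing of eligibility criteria is protocol content, and this item is stated in a form that cannot work with the article's own schedule. That is a misfit in what is written, not detail left out.

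A second reply is that nothing in the article suggests feeding messages would change the frequency of birth trauma. Removal by a rule applied blind would then be equal in expectation and cause no systematic bias. This also stands, and it is why the bias can be zero. The article, however, gives no such rule.

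A reader might infer more than the documents support:

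- **That unblinded staff will decide the removals.** The research assistant is unblinded, but nobody is named as applying this criterion. NICU admission is a clinical decision, and the blinding of clinicians is not described. Arm-aware judgment is not ruled out, but it is not stated.
- **That several criteria share the defect.** Only the birth-trauma item certainly does.
- **That EBF in an arm would move from 48% to 50.5% or 53.3%.** Those values (0.48/0.95 and 0.48/0.90) require 5% or 10% removal in that arm with every removed infant an EBF failure. They are worst cases.
- **That the trial would be underpowered** because the 20% loss allowance names only withdrawal and app discontinuation. The surplus in 300 absorbs the loss.
- **That dyads have already been dropped.** The article reports none.

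**Conclusion.** The point holds for one criterion. Birth trauma leading to NICU admission cannot be judged at the baseline screen, and using it later contradicts the analysis of all participants as randomized. Referral needs a time point. Preeclampsia is sound as a baseline screen.

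The harm is to validity and clarity, not to power, which remains at 83% or more for removal of up to 15%. The size of any bias cannot be derived from the documents. The range of about 1 to 2.5 points, against a 20-point target, rests on assumed removal rates, assumed EBF among removed dyads, no true effect and unequal removal. With equal removal unrelated to arm it is zero. The range concerns EBF; the documents give no basis for a corresponding figure for AACF.

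The point is timely. The abstract reports recruitment from February 2, 2026, with 241 women enrolled by May 18. Women enrolled first at 36±1 weeks will have delivered by then, so the criterion may already have come into play. No 6-month assessment could yet be due: even a birth on the first recruitment day reaches 6 months only in early August, or about two weeks earlier with the visit window.

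**What to change.** Amend the wording as follows:

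1. State that eligibility is judged only on facts known before the envelope is opened.
2. Delete the birth-trauma item from the exclusion list.
3. Limit referral and preeclampsia to the woman's status at baseline.
4. State that every randomized dyad stays in follow-up and in the intention-to-treat set whatever happens at or after birth. If any dyad has been dropped for this reason, resume its follow-up, subject to consent.

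A sensitivity analysis without dyads affected by birth trauma is optional. If done, it should use a written rule applied blind to arm.

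These changes concern study eligibility and analysis only, not care of the mother or infant. The cost is an amendment approved by the ethics committee and continued contact with what is likely to be a small number of dyads, for which the telephone follow-up already allowed under Follow-Up can serve. The downside is slight dilution of the effect by infants whose feeding was affected by illness.

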### Sample Size

The sample size was calculated to detect a 20% absolute difference in the primary outcomes between the intervention and control arms. The calculation assumed a baseline prevalence of EBF of 48% [3] and AACF of 50% [39] in the control group. Using a 2-sided significance level of 5%, statistical power of 80%, a 1:1 allocation ratio, and an anticipated 20% loss to follow-up in each study arm, a total sample of 300 pregnant women (150 per arm) was determined to be sufficient to detect the expected intervention effect. Loss to follow-up included participant withdrawal and/or discontinuation of app use in the intervention arm. Sample size estimation was performed using *OpenEpi* software (version 3.0).

### Recruitment

Participants who have given consent will be recruited through purposive sampling by the research assistant (RA). Informed consent will be taken in a private room at the obstetric clinics. Purposive sampling will ensure that participants meet the technology-specific eligibility criteria, which are essential for valid effect estimation [40]. Importantly, randomization will occur after purposive recruitment to preserve internal validity.

### Randomization and Allocation Concealment

Participants will be randomly assigned in a 1:1 ratio to the intervention or control arm using a computer-generated block randomization sequence prepared by the AKUH Clinical Trials Unit. Allocation concealment will be ensured using opaque, sealed, and sequentially numbered envelopes containing group assignments. The envelopes will be opened sequentially after participant enrollment to ensure concealed allocation and minimize selection bias.

### Blinding and Bias Minimization

Due to the nature of the intervention, blinding of participants and the RA is not feasible. To minimize observer and reporting bias, standardized outcome assessment procedures will be implemented across both study arms. The RA will receive training on neutral interviewing techniques and adherence to standardized counseling scripts to reduce differential probing or influencing participant responses. Structured questionnaires will be used to ensure consistency and reduce subjective interpretation during outcome assessment. In addition, data analysis will be conducted using coded group allocation to minimize analytical bias.

### Intervention

#### Pehli Ghiza (First Diet) mHealth App

Participants randomized to the intervention arm will receive educational awareness through the Pehli Ghiza mHealth app. This is in addition to routine standard-of-care F2F counseling delivered to all participants in both arms at each follow-up visit. The inclusion of standard of care will allow for the evaluation of the incremental effect of the intervention, such that any observed between-group differences can be attributed to the intervention rather than to the standard of care.

#### Theoretical Framework

The intervention design and messaging were informed by self-determination theory [41], which posits that sustained behavior change is facilitated when 3 basic psychological needs of autonomy, competence, and relatedness are supported. Fulfillment of these psychological needs promotes internalization and autonomous motivation, thereby increasing the likelihood of adopting, adhering to, and maintaining optimal IYCFPs over time (Figure 2). The messages were designed to align with these constructs (Table 1). *Autonomy* was addressed by providing mothers with a meaningful rationale for recommended IYCFPs, practical options, and support to overcome feeding barriers. *Competence* was supported through skill-based educational content, videos for practical guidance, and reinforcement reminders aimed at improving mothers’ confidence and ability to adopt optimal feeding practices. *Relatedness* was promoted by delivering supportive and culturally sensitive messages intended to foster trust, understanding, and a sense of connection with the intervention.

**Figure 2. F2:**
[figure not shown]
Theoretical framework summarizing the application of pillars of self-determination theory to the development of mobile health content. IYCF: infant and young child feeding; mHealth: mobile health.

**Table 1. T1:** Examples of infant and young child feeding practices messages aligned with self-determination theory constructs of autonomy, competence, and relatedness.

Feeding stage	mHealth^a^ messages^b^	Objectives	Autonomy	Competence	Relatedness
Pregnancy	What you eat lays the foundation of a healthy child. Eat fresh fruits and vegetables, drink plenty of water, and avoid excess consumption of tea, coffee, and processed food Do not forget, breastfeeding is the best gift a mother can give to her newborn Breastfeeding can lead to long-term health benefits for infants, such as a reduced risk of asthma, obesity, and type 1 diabetes	Generate willingness to improve and maintain healthy dietary habits and motivation for breastfeeding during pregnancy	Getting an insight into one’s own current personal dietary choices in an autonomous way, with little external control	Feeling confident to change diet patterns	Reflect upon dietary practices
EIBF^c^	Do not waste the yellow milk produced soon after delivery. Feed it to the baby, as it contains essential nutrients and protection against diseases.	Foster motivation to perform EIBF	Self-awareness without external control about the importance of EIBF	Feeling confident toward learning the skill of breastfeeding	Being at ease to learn the breastfeeding skill
EBF^d^	Your baby needs only breast milk for the initial 6 months, as it fulfills all food, water, and energy requirements It is important to drink water regularly and eat healthy food like eggs, meat, lentils, yogurt, milk, fresh fruits, and vegetables. It keeps you healthy, strong, and improves your milk flow	Develop commitment to maintain EBF for 6 months Create mindfulness regarding the importance of maternal diet while nursing	Provide self-confidence to perform and maintain EBF in an autonomous way, not imposed	Feel confident to maintain the learned behavior of EBF	Ready to improve breastfeeding skill
CF^e^ (6 to 12 mo)	Your baby, at 6 mo of age, requires healthy foods in addition to breast milk to grow and develop Continue breastfeeding on demand both day and night Begin with the staple foods like porridge (wheat, rice), mashed banana, or mashed potato Give 2 to 3 tablespoonfuls to taste at each feed Give food at least 2 times a day	Expand readiness to establish CF while maintaining an intention to continue breastfeeding till 2 years of age	Develop a plan to best maintain breastfeeding along with CF independently, without coercion	Feel confident to initiate a healthy complementary diet and maintain breastfeeding	Reflect to learn, improve, and maintain optimum CF practices

a mHealth: mobile health.

b Messages are adapted from [42].

c EIBF: early initiation of breastfeeding.

d EBF: exclusive breastfeeding.

e CF: complementary feeding.

#### Content Development

Initial formative research with the target population informed the design of the *Pehli Ghiza* mHealth app and guided the contextual adaptation and appropriateness of its content and delivery to locally identified barriers and facilitators related to IYCFPs. The educational content, based on WHO and UNICEF (the United Nations Children’s Fund) IYCF guidelines [43-45] and AKUH educational materials [46], focused on maternal nutrition, breastfeeding, CF, child immunization, and early growth and development. Specific and brief messages, tailored according to maternal gestational stage and infant age, were developed for dissemination through the mobile app. Messages were initially developed in English, translated into Urdu, and subsequently back-translated to ensure linguistic accuracy and consistency. The messages were reviewed and content validated by lactation and nutrition experts for scientific accuracy, clarity, and contextual appropriateness. The intervention messages and app interface were pilot tested among the target population prior to implementation, and participant feedback was incorporated to improve usability and acceptability.

#### Messages Delivery Format

Tailored educational messages, adapted to maternal gestational stage and infant age, will be delivered in the form of short text messages and brief videos of approximately 2 minutes in duration (Figure 3). This format is designed to maintain attention, enhance engagement, and reduce cognitive burden among participants.

**Figure 3. F3:**
[figure not shown]
*Pehli Ghiza* (First Diet) mobile health app screenshots showing the logo, sign-in credentials, welcome note, messages contextualized according to the predelivery, delivery, and postdelivery stages, and library access to archived messages and videos.

